## Abstract

**Rationale:**

Detection of atrial fibrillation (AFib) and subsequent anticoagulation therapy reduce the risk of recurrent stroke, while prolonged rhythm monitoring significantly increases AFib detection. Thus, prolonged smartwatch-based ECG monitoring after cryptogenic ischemic stroke or transient ischemic attack (TIA) could lead to a reduction of recurrent stroke by prompting adequate anticoagulation therapy.

**Aim:**

WATCH AFib investigates the accuracy of smartwatches for AFib detection in patients with cryptogenic TIA or ischemic stroke compared to an implantable event recorder.

**Sample size:**

40 cases of AFib are required to estimate the sensitivity for AFib detection per patient with a precision of about 10%. As AFib is observed in 9%−16% of cryptogenic strokes, we intend to enroll 400 patients.

**Methods:**

WATCH AFib is a prospective, intraindividual-controlled, multicentre clinical study in patients with cryptogenic ischemic stroke or TIA. ECG-data from smartwatches and event recorders is continuously monitored by two independent cardiologists for a follow-up period of 6 months. If AFib is detected, therapeutic options are discussed at the including center.

**Primary outcome:**

To compare smartwatch- and event recorder- based sensitivity and specificity of AFib detection per patient after 6 months.

**Discussion:**

Prolonged AFib screening after stroke is currently suboptimal. Smartwatches might be a non-invasive, cost-effective, widely available alternative for prolonged rhythm monitoring. Usability in severely affected patients and patients with persisting neurological deficits might be limited.

**Trial registration:**

The study is registered on clinicaltrials.gov. Registration number: 20230726.

## Introduction

1

In the secondary prevention of ischemic stroke, detection of atrial fibrillation (AFib) and subsequent anticoagulation therapy reduce the risk of recurrent stroke by approximately 60% (1, 2). Cryptogenic stroke is defined as ischemic stroke for which no probable cause is found despite a full standard evaluation and comprises 25% of all ischemic strokes (3). Prolonged electrocardiogram (ECG) monitoring for 30 days to 6 months significantly increases detection of occult paroxysmal AFib, which is present in 9%−16% of cryptogenic strokes (4–7). Careful patient preselection can increase detection rates up to 28% in 6 months (8). A meta-analysis of 1,102 patients revealed that prolonged ECG monitoring after ischemic stroke correlates with higher detection rates of paroxysmal AFib, initiation of anticoagulant therapy, and decrease of stroke recurrence (9). Thus, prolonged ECG monitoring is likely to lead to a reduction of recurrent stroke by prompting adequate anticoagulation therapy.

Still, the most efficient and cost-effective way of rhythm monitoring after a cryptogenic stroke is unclear (10–12). In addition, prolonged AFib screening using implantable cardiac monitors (ICM) is currently suboptimal due to a limitation of resources, loss to follow-up, invasiveness of procedures, and costs (13). A fast growing body of evidence in the field of cardiology states that smartwatches detect AFib with similar sensitivity and specificity to other wearable devices (i.e., Holter- ECGs and others) and ICMs. Continuous derivation of photoplethysmography (PPG)- signals by a smartwatch has been shown to sufficiently detect AFib in the general population with a positive predictive value of 0.84–0.98 (14–16). Similarly, comparing PPG-based to in hospital ECG-based diagnosis, sensitivity and specificity of AFib detection is high (93%−98% and 90%−98%, respectively) (17–19). Compared to implantable cardiac monitors, PPG- based AFib diagnosis exhibits a sensitivity of 97.5% for AFib episodes >1 h and a sensitivity of 100% for AFib detection per patient (18). Current generations of smartwatches are further able to perform a patient activated one-lead ECG, which shows good sensitivity (93.5, 94.4%) and specificity (100, 81.9%) compared to 12-lead ECG monitoring (20, 21) and may enhance diagnostic accuracy by combination of both methods. Nevertheless, a high number of inconclusive recordings after automated analysis (20%−30%) constitutes a limitation, and can be overcome by cardiologist review (20–22).

Recently, it could be shown that patient acceptance of smartwatches (Pulsewatch) for AFib detection in stroke patients >50 years of age is high (23, 24). Up to now, only one study compares smartwatches to ECG patches for 14 + 30 days in stroke survivors and concludes that smartwatches are feasible for long-term arrhythmia monitoring. Nevertheless, as AFib was detected in only five patients, and the follow-up period was relatively short, the results of the study are preliminary (24). Further studies are urgently needed to address the existing lack of evidence.

As stroke patients often suffer from relevant disabilities, a transfer from the hitherto existing data about AFib and smartwatches from otherwise healthy individuals cannot be assumed. To our knowledge, there is only one other ongoing study assessing the accuracy of smartwatch-derived PPG signal for AFib detection in a stroke population under real-life circumstances (NCT05006105). So far, the protocol or final results have not been published.

We hypothesize that AFib detection via smartwatch in patients suffering from cryptogenic transient ischemic attack (TIA) or ischemic stroke is accurate for AFib detection compared to an implantable Event Recorder and hence introduce the following prospective multi-center clinical trial (WATCH AFib). If our hypothesis proves right, smartwatches might be a non-invasive, cost-effective, widely available alternative for rhythm monitoring, which could potentially change the current standard of post-stroke care.

## Methods and analysis

2

### Study design

2.1

The clinical study is carried out in accordance with the study protocol and the principles of the Declaration of Helsinki by the World Medical Association and specific applicable national ethical and regulatory requirements. The study was approved by the local ethics committee.

We conduct a prospective, intraindividual-controlled, multicenter clinical study, as depicted in Figure 1. The study population includes patients with cryptogenic TIA or ischemic stroke and known risk factors for the presence of paroxysmal AFib (see inclusion criteria). As participants are recruited multi-centric and nationwide, it is expected that results are representative for the German/European ischemic stroke population and are transferable to the general population with TIA or ischemic stroke. As no strong recommendation on the selection of stroke patients for event recorder implantation exists, and as the event recorder is not part of the study intervention, we do not specify selection criteria for implantation.

**Figure 1 F1:**
[figure not shown]
Study flowchart.

Patient screening and inclusion are performed at selected study centers according to the defined inclusion and exclusion criteria (see below). Standardized onboarding training, printed guides, and caregiver assistance documentation are provided for all study sites. The study centers hold cross-regional stroke units treating >1,000 patients with ischemic stroke or TIA per year and collaborate with cardiologists experienced in implantation of event-recorders. All patients included in the clinical study will receive standard of care for cryptogenic TIA/ischemic stroke. The study intervention consists of wearing a smartwatch (i.e., Scanwatch, Withings), which is CE-certified as medical device for AFib detection. Smartwatch- and Event Recorder-derived heart rhythm are daily uploaded and analyzed by cardiologists at the Cardiology Core Lab at the Department of Internal Medicine I, TUM Klinikum Rechts der Isar, Munich. Obtained data on cardiac arrhythmia will be accessible for each study site in consultation with the Cardiology Core Lab. In case of AFib detection (defined as arrhythmia lasting longer than 30 s), the including study site will be informed to set an *ad-hoc* detection visit and determine further therapeutic options. The study also includes a total of four pre-scheduled visits, to confirm eligibility, to record stroke and patient characteristics, smartwatch application and usability, stroke recurrence and adverse events (see Table 1). The baseline visit (Visit 0) may take place within the clinical setting of the acute stroke work up. The second and third visit (Visit 1, Visit 2) constitute phone-visits at 1 and 3 months. The last visit at the end of the study (Visit 3) will be performed at 6 months. In-patient visits will take place at each patient's study center.

**Table 1 T1:** Data to be collected.

**Data to be collected**	**Visit 0**	**Visit 1^¥^**	**Visit 2^¥^**	**Visit 3**	**Detection visit**
	**Max. 6 months after stroke/TIA**	**1 month** ±**1 week**	**3 months** ±**1 week**	**6 months** ±**3 weeks**^#^	**If AFib is confirmed**
In-/exclusion criteria^a^	X				
Patient characteristics^b^	X			X	
Stroke characteristics^c^	X				
Physical examination^d^	X			X	
NIHSS	X			X	
mRS	X	X	X	X	
Application of smartwatch^e^		X	X	X	
Stroke/TIA recurrency		X	X	X	
AESI/device incidents		X	X	X	
Detection of AFib^f^					X
Study termination				X	

^a^See methods.

^b^Includes age, sex, medical history, and cardiac risk factors on echocardiography (TTE/TEE).

^c^Includes date of index event, vascular occlusion and site of occlusion, application of intravenous thrombolysis or mechanical thrombectomy, NIHSS at initial presentation, premorbid mRS, mRS at initial presentation, discharge.

^d^Includes date of examination, impaired hand-/arm function on the dominant limb, neglect, hemianopsia, apraxia, aphasia.

^e^Includes hours of daily application, nightly application, comfort, user friendliness.

^f^Date of visit, visit location, evaluation of oral anticoagulation and possible further medical/interventional treatment.

^¥^Phone visit.

^#^Or in case of premature termination of the study.

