#### Primary objectives

2.2.1

The primary objective is to assess whether AFib detection via smartwatch in patients suffering from cryptogenic TIA/ischemic stroke is accurate in comparison to implantable event recorders. This will be assessed by sensitivity and specificity of AFib detection per patient after 6 months. We aim on a comparison of smartwatch based, continuous, automated, cardiologist supervised rhythm analysis of photoplethysmography (PPG)- signal and patient activated one-lead ECG with event recorder based, continuous, automated ECG rhythm analysis.

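### The article does not state that the watch is read masked to the recorder, or how watch findings made after a recorder-triggered visit count toward 6-month sensitivity

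*Protocol article*

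**What the plan says.** All places are in the protocol article.

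- **Who reads.** Section 2.1 (Study design): "Smartwatch- and Event Recorder-derived heart rhythm are daily uploaded and analyzed by cardiologists at the Cardiology Core Lab". The abstract (Methods) adds: "ECG-data from smartwatches and event recorders is continuously monitored by two independent cardiologists for a follow-up period of 6 months". This is the only statement on reader independence.
- **What the watch test is.** Section 2.2.1 defines it as "continuous, automated, cardiologist supervised rhythm analysis of photoplethysmography (PPG)- signal and patient activated one-lead ECG". Section 2.5 makes the cardiologist-supervised recorder analysis the gold standard and lets it prevail when the devices disagree. Reader judgement therefore enters both sides of the comparison.
- **What happens on detection.** Section 2.1: on AFib detection (arrhythmia of more than 30 s) "the including study site will be informed to set an" ad-hoc detection visit. Table 1, footnote f, lists among the items for that visit "evaluation of oral anticoagulation and possible further medical/interventional treatment". The trigger is not restricted to one device or deferred to month 6. Section 2.1 also says: "Obtained data on cardiac arrhythmia will be accessible for each study site in consultation with the Cardiology Core Lab".
- **How the watch is scored.** Section 2.2.1: "This will be assessed by sensitivity and specificity of AFib detection per patient after 6 months".
- **Related analyses.** Section 2.2.3 lists, as secondary objectives, per-patient accuracy from automated PPG alone, accuracy for any AFib episode, sensitivity for episodes over 1 h, and accuracy per recorded or analyzable time.

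**The concern.** The trial asks whether a watch could serve as an alternative to an implanted recorder, so the watch has to find AFib without the recorder's help. As described, that help could enter in three ways.

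1. **Reading.** A cardiologist who knows that the recorder has shown AFib may classify a doubtful watch signal differently. The Introduction gives the room for this: 20% to 30% of watch ECG recordings are inconclusive after automated analysis and are left to cardiologist review.
2. **Disclosure.** A patient called in after a recorder detection may record more watch ECGs, or may receive treatment that reduces later AFib. The watch result is still taken over the full 6 months.
3. **Timing.** A per-patient result over 6 months, with no stated matching in time, would let a watch false alarm in one month count as a true positive because the recorder found AFib in another.

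The first way depends on how the readers are organised. The second follows from the stated notification flow and the stated measure, and remains even if the readers are fully masked. The third also remains under masking.

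**Working it through.** **Step 1: the plan's own precision.** Inputs from section 2.4: 40 AFib cases among 400 patients, assumed sensitivity above 99%, assumed specificity 90%, two-sided exact 95% interval, precision = point estimate minus lower bound.

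| Quantity | Lower bound | Precision | Plan states |
|---|---|---|---|
| Sensitivity, 40/40 | 91.2% | 8.8 points | about 10% |
| Sensitivity, 99% of 40 | 89.3% | 9.7 points | about 10% |
| Sensitivity, 39/40 | 86.8% | 10.7 points | about 10% |
| Sensitivity, 35/36 (10% drop-out) | 85.5% | 11.8 points | 12% |
| Specificity 90%, n = 360 | 86.4% | 3.6 points | 4% |
| Specificity 90%, n = 324 (10% drop-out) | 86.2% | 3.8 points | 4% |

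The plan's figures are reproduced and are not in dispute. They describe random error and do not cover the shift discussed here.

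**Step 2: weight of one patient.** 1/40 = 2.5 points of sensitivity. Suppose the trial observes 40/40, but k patients are watch-positive only because of the recorder (k is an assumption). Unaided sensitivity is then (40 − k)/40:

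| k | Unaided sensitivity | Exact 95% interval |
|---|---|---|
| 0 | 100% | 91.2 to 100 |
| 1 | 97.5% | 86.8 to 99.9 |
| 2 | 95.0% | 83.1 to 99.4 |
| 4 | 90.0% | 76.3 to 97.2 |

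Four such patients equal the whole planned precision of about 10 points.

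**Step 3: limit on the upward shift.** Only misses can be upgraded. If true unaided sensitivity is s and a share q of the misses is credited, apparent sensitivity is s + q(1 − s).

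- s = 0.99: expected misses are 0.01 × 40 = 0.4 patients, so the expected upward shift is at most 1 point.
- s = 0.90, q = 0.5: 0.90 + 0.5 × 0.10 = 0.95. With q = 1 it is 1.00.

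The downward shift is not limited in this way. A patient in whom the watch would have found AFib later, but in whom treatment removes that AFib, costs 2.5 points whatever s is.

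**Step 4: time matching alone.** Take the plan's 90% specificity as a 10% chance of a false alarm per patient over 6 months. Assume that it applies equally, and independently of true detection, in patients with AFib. Apparent sensitivity is then s + 0.10(1 − s):

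- s = 0.99: 0.99 + 0.10 × 0.01 = 0.991, a shift of 0.1 point.
- s = 0.80: 0.80 + 0.10 × 0.20 = 0.82.
- s = 0.50: 0.50 + 0.10 × 0.50 = 0.55.

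The values 0.80 and 0.50 are illustrations and do not come from the article. Low values are conceivable in the full analysis set, where section 2.5 counts missing watch data as no AFib signal, or in the impaired subgroups of section 2.2.2.

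**The case against.** A reader might infer that the two results are demonstrably not independent, or that one person reads both devices. The article does not say so. One core lab is not one reader, and two independent cardiologists could mean one per device just as well as two for both streams. The article condenses a fuller protocol, which may define readers' roles and scoring rules. Masking is unstated, not denied. This part of the objection stands.

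A reader might also infer that the bias runs upward. That is not shown either. Treatment after a detection can lower later watch findings, the listed content of the detection visit does not include extra watch ECGs, and PPG is continuous, so detection does not rest on prompted recordings alone. At the plan's own 99% there is little left to inflate.

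The secondary analyses help in part. Automated PPG removes the watch reader and the patient-activated ECG, and the episode-level and time-level analyses imply alignment with the recorder. But they are not primary, and none of them undoes the effect of a detection visit.

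Finally, it is tempting to replace the primary definition by overlapping, pre-disclosure detections. That would change the question. The watch window would close at the first disclosed recorder finding in patients with AFib, possibly within days given daily upload, while the others keep 6 months. A genuine, unaided later detection would become a miss. This supports a supplementary analysis, not a replacement.

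What remains is that detections are acted on during follow-up, the watch is scored over the whole period, and the article gives no rule for watch findings in between.

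**Conclusion.** The concern holds as an open question of bias in the primary sensitivity, and should be settled before the data are read. The stated rules allow knowledge of the recorder to reach the watch result through the detection visit. They may also allow it through the reader, because masking is not stated. The direction is uncertain. The size is 2.5 points per affected patient at 40 cases, and four patients would use up the planned precision; the number affected is an assumption that the article cannot inform. The part due to time matching is about 0.1 point under the plan's assumptions and matters only if true sensitivity is well below them. The sample size needs no change. Watch readings made with knowledge of the recorder cannot be undone at analysis, which is the reason to act early.

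**What to change.** 1. State that each device's signal is classified by a cardiologist masked to the other device and to detection visits. The two existing readers suffice.
2. Time-stamp each watch reading and lock it when it is made.
3. Leave site notification as it is.
4. Keep the 6-month per-patient primary measure. Beside it, prespecify a per-patient sensitivity analysis that credits a watch detection only if it overlaps recorder-confirmed AFib and began before the recorder finding was disclosed. Report later watch detections separately.

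The cost is a core-lab work instruction, separate worklists per device and one additional analysis rule, with no new procedure for patients. If both cardiologists now read both streams, assigning one to each device gives up double reading. The stricter analysis may show a lower sensitivity, and should be presented with the caveat that it shortens the watch window in patients with AFib only.

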#### Inclusion criteria

2.1.1

Event recorder with telemedicinal function, implanted at the discretion of the attending physician.Cryptogenic stroke, or TIA with definite cortical syndrome (aphasia, neglect or homonymous hemianopia) within the last 6 months after full standard evaluation:
Stroke detected by computed tomography (CT) or magnetic resonance imaging (MRI) that is not lacunar (lacunar is defined as a subcortical infarct in the distribution of the small, penetrating cerebral arteries whose largest dimension is ≤ 1.5 cm on CT or ≤ 2.0 cm on MRI diffusion images),Absence of extracranial or intracranial atherosclerosis causing ≥50 percent luminal stenosis of the artery supplying the area of ischemia,No major-risk cardioembolic source of embolism (i.e., no permanent or paroxysmal atrial fibrillation, sustained atrial flutter, intracardiac thrombus, prosthetic cardiac valve, atrial myxoma or other cardiac tumors, high-grade mitral valve stenosis, recent (within 4 weeks) myocardial infarction, left ventricular ejection fraction < 30 percent, valvular vegetations, or infective endocarditis),No other specific cause of stroke identified (e.g., arteritis, dissection, migraine, vasospasm, drug abuse),No paroxysmal atrial fibrillation in 72 h of in-hospital ECG-monitoring, including at least one Holter- ECG for 24 h.Age: ≥40 years.At least one of the following risk factors:
CHA2DS2VASc score ≥4,Atrial runs ≥20 consecutive supraventricular premature beats,Left atrial size > 45 mm,Left atrial appendage flow ≤ 0.2 m/s.No contraindication for anticoagulant therapy after acute phase of stroke.Written informed consent by patient or authorized caregiver.

#### Exclusion criteria

2.1.2

Patient is not able to perform one-lead ECG recording with smartwatch,Patient possesses no smartphone (iOS version 15.0 or later; Android 9 or later),Implanted pacemaker or cardioverter defibrillator (ICD),Pregnancy or breastfeeding period.

### Objectives

2.2

#### Primary objectives

2.2.1

The primary objective is to assess whether AFib detection via smartwatch in patients suffering from cryptogenic TIA/ischemic stroke is accurate in comparison to implantable event recorders. This will be assessed by sensitivity and specificity of AFib detection per patient after 6 months. We aim on a comparison of smartwatch based, continuous, automated, cardiologist supervised rhythm analysis of photoplethysmography (PPG)- signal and patient activated one-lead ECG with event recorder based, continuous, automated ECG rhythm analysis.

#### Subgroup analyses

2.2.2

As smartwatch usability might be impaired for patients with residual neurological deficits or severely affected patients, we predefine the following analyses for this clinically relevant subgroups:

Sensitivity and specificity for AFib detection in patients with residual neurological deficit (aphasia, apraxia, hemianopsia, neglect, or a hemiparesis on the dominant extremity)Sensitivity and specificity for AFib detection in severely affected patients (i.e., NIHSS ≥8).

#### Secondary objectives

2.2.3

Positive and negative predictive values for AFib detection per patient within 6 monthsSensitivity and specificity for AFib detection per patient based on automated PPG-signal rhythm analysisSensitivity and specificity for the detection of any AFib episodeSensitivity for the detection of AFib episodes >1 hSpecificity for episodes of sinus rhythm >1 hSensitivity and specificity of AFib detection per recorded/per analyzable time (i.e., intervals in which the watch is actually worn/records an analyzable signal)Ischemic stroke and TIA recurrence within 6 months.

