### Sample size estimation

2.4

According to a previous study a sensitivity and specificity for AFib detection per patient of >99 and 90%, can be assumed, respectively (18). Thus, 40 cases of AFib are required to estimate the sensitivity with a precision of about 10%, i.e., the difference of the lower bound of a two-sided exact 95% confidence interval and the point estimate of the sensitivity is 10%. As other studies observe paroxysmal AFib in 9%−16% of patients with cryptogenic stroke (4, 5), we intend to enroll 400 patients to obtain the required 40 cases. The specificity can consequently be measured with a precision of 4%. Our inclusion criteria should lead to a preselection of candidates with increased AFib risk factors. Therefore, AFib detection rate might increase up to 28% (max = 112) in our cohort within 6 months (8). The event of a 10% drop-out rate (e.g., due to withdrawal of consent, eligibility violations, no intervention, or non-existent data after inclusion into the study) would result in a minimum of 36 AFib cases and a similar precision of estimation i.e., 12% for the sensitivity and 4% for the specificity.

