### Statistical methods and analysis populations

2.5

Point estimates and two-sided exact 95% confidence intervals will be computed for the sensitivity and specificity referring to the primary objectives, related secondary objectives and subgroup analyses. Cardiologist-supervised event recorder-based continuous ECG rhythm analysis serves as the gold standard. Thus, in the case of discordant results, we consider the analysis of the signal from the event recorder by the cardiologist as the true status. As power calculation is based on participants with detected AFib as effective sample size (n_AFib_), we intend on analyzing our data as soon as one of the following situations occurs: (1) AFib is detected in 40 participants, who have completed follow-up or (2) enrolment and follow up is complete for all 400 participants (n_Enrolment_). In the first situation, the study leadership, the statistician, and the steering committee will decide on continuation of enrolment. Exploratory hypothesis testing of comparisons will be performed by McNemar's Chi-squared Test at two-sided 5% levels of significance. Due to the exploratory character of the analysis, and in accordance with the calculation of 95% confidence intervals, there will be no correction for multiple testing. With reference to the ICH E9 Guideline, the analyses will be performed using a full analysis set (FAS), according to the intention-to-treat principle (ITT), and a per protocol set (PP). The former will include all times with event recorder measurements (until possible but unexpected losses to follow-up) and the latter will include only times with additional smartwatch recordings. Therefore, missing values, possibly due to non-compliance, will be rated as no signal of an AFib by the smartwatch in the FAS. The FAS and PP analysis populations coincide when smartwatch records are available in all patients. Patients with eligibility violations (concerning inclusion or exclusion criteria), no intervention or non-existent data after inclusion into the study will be excluded from analysis. Time to confirmed AFib diagnosis, count of AFib diagnoses, AFib burden, safety endpoints and usability of smartwatches will be reported by descriptive statistics (mean, standard deviation, median, interquartile range, absolute and relative frequency). AFib risk factors will be compared between patient groups with and without AFib using descriptive statistics, hypothesis testing and multiple logistic regression models. Pre-defined subgroup analyses will be performed as described above.

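### Specificity for detecting any AFib episode has no countable AFib-free unit, so its value depends heavily on the time unit chosen; a false-alarm rate and an episode-level predictive value should replace it

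*Protocol article*

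**What the plan says.** The protocol article's Secondary objectives (2.2.3) list accuracy on several scales: per patient, per episode, and by recorded or analyzable time. Two of the entries are specificities on an episode scale:

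- sensitivity and "specificity for the detection of any AFib" episode;
- specificity "for episodes of sinus rhythm" longer than 1 h.

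The time-based specificity is a separate entry, so the first item must mean something other than that.

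Statistical methods and analysis populations (2.5) fixes how such figures are reported: "Point estimates and two-sided exact 95% confidence intervals will be computed for the sensitivity and specificity referring to the primary objectives, related secondary objectives". The predefined subgroups are treated the same way.

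Study design (2.1) defines the positive event as arrhythmia of more than 30 s. The article does not say what counts as one AFib-negative unit when the target is any AFib episode. The primary objective (2.2.1) is per patient, so its unit is clear.

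**The concern.** Specificity is TN/(TN + FP). An AFib episode is an event with a start and an end, and episode-level sensitivity has a natural denominator, namely the recorder's episodes. There is no matching list of non-episodes. True negatives exist only after follow-up time has been cut into units, and the shorter the unit, the more true negatives there are for the same false alarms.

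An exact binomial interval adds a precise-looking range to a figure whose denominator the objective does not determine. Two analysts with identical data could report different specificities, and the result could not be compared with other studies. The number of false alarms per month of wear bears on whether watch monitoring is workable after stroke, and this figure would not convey it.

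**Working it through.** **Inputs from the plan** (Sample size estimation, 2.4): "a sensitivity and specificity for AFib detection per patient of >99 and 90%, can be assumed, respectively"; "we intend to enroll 400 patients to obtain the required 40 cases", which leaves 400 − 40 = 360 patients without AFib; 6 months of follow-up.

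**The plan's own figure.** With 324 of 360 AFib-free patients correctly negative (90%), the exact 95% lower bound is 86.4%, a distance of 3.6 points. This agrees with the statement "The specificity can consequently be measured with a precision of 4"%. The per-patient specificity has a clear unit and its precision reproduces.

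**Step 1: same watch, different units.** Assume a constant false-alarm rate λ in AFib-free time.

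- Hours in 6 months: 6 × 30.4375 × 24 = 4,383.
- λ = −ln(0.90)/4,383 = 2.404 × 10⁻⁵ per hour.
- Specificity for a unit of u hours = exp(−λu).

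| Unit | u (h) | Specificity |
|---|---|---|
| day | 24 | 99.94% |
| hour | 1 | 99.998% |
| 30 s | 1/120 | 99.99998% |

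Direct counting gives the same picture. Assume 36 of the 360 patients have one false alarm each over 182 days of full wear. Then 36 alarms in 65,520 patient-days gives 99.945%, in 1,572,480 patient-hours 99.998%, and in 188,697,600 windows of 30 s 99.99998%.

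**Step 2: what the listed measures can and cannot show.** Keep the same 36 patients, but let each have 1, 10 or 50 false alarms, with at most one alarm per unit. The rate is total alarms divided by 1,572.48 thousand hours. For the predictive value, assume one recorder episode in each of the 40 AFib patients, all found by the watch, so PPV = 40/(40 + alarms).

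| Alarms per affected patient | Total | Per-patient specificity | Daily units | Hourly units | Alarms per 1,000 h | Episode PPV |
|---|---|---|---|---|---|---|
| 1 | 36 | 90.0% | 99.945% | 99.998% | 0.023 | 52.6% |
| 10 | 360 | 90.0% | 99.45% | 99.977% | 0.23 | 10.0% |
| 50 | 1,800 | 90.0% | 97.25% | 99.886% | 1.14 | 2.2% |

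Per-patient specificity does not move, because it counts a patient once. Hourly specificity moves only in the second decimal place of the percentage or nearby. The rate and the predictive value separate the three cases plainly.

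**Step 3: sinus rhythm >1 h.** This objective names a unit with a minimum length but no maximum and no splitting rule. Suppose each unbroken stretch counts once. Each of the 360 AFib-free patients then supplies one unit, and each of the 40 AFib patients with k episodes (an assumed number) supplies k + 1 equal stretches. Pooled specificity = [360 × 0.90 + 40(k+1) × exp(−λ × 4,383/(k+1))] / [360 + 40(k+1)].

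- k = 5: (324 + 235.8)/600 = 93.3%
- k = 20: (324 + 835.8)/1,200 = 96.6%
- k = 100: (324 + 4,035.8)/4,400 = 99.1%

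Consecutive blocks of about an hour would give about 99.998%. The watch is the same throughout.

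**The case against.** The strongest reply has four parts.

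**An analysis plan that is not shown may define the unit.** This stands for the sinus-rhythm objective: it names its unit, and a splitting rule is the kind of detail an analysis plan supplies. It does not fully answer the point about any AFib episode. There the chosen measure has no negatives of its own, and a window added later turns it into a window-based measure, which the objective should say.

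**Other endpoints would expose a poor watch.** This largely stands. A reader might infer that a watch with many false alarms could pass as near-perfect. Take one false alarm per patient-month: hourly specificity would be exp(−1/730.5) = 99.86%, but only exp(−6) = 0.25% of AFib-free patients would have none. The primary specificity would collapse, and the listed per-patient predictive value would suffer too. What remains is narrower. Per-patient measures count one alarm and fifty alike, time-based specificity reflects the duration of false AFib rather than the number of alarms, and the exploratory count of AFib diagnoses is not tied to disagreement with the recorder.

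**The range is illustrative.** This stands. A reader might infer that both objectives can run from 90% to above 99.99%. The 90% end is the plan's per-patient assumption with six months treated as one unit, and a 30-s unit cannot apply to the >1 h objective. The constant rate and the episode counts are assumptions. Once a unit is fixed, the figure does reflect the watch: the two hourly values, 99.998% and 99.86%, differ about 57-fold in false-positive proportion (1/730.5 against 2.404 × 10⁻⁵).

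**Atrial runs.** Because "runs ≥20 consecutive supraventricular premature beats" is one of the qualifying risk factors, a reader might infer that false alarms cluster in such rhythms and that a sinus-only denominator misses them. The documents do not say where false alarms fall, so this is no part of the point.

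**Conclusion.** The point holds for one secondary objective. Specificity for any AFib episode is ill-posed as worded, because it has no countable negatives. Under a constant false-alarm rate matched to the assumed 90% per-patient specificity, it would read 99.94%, 99.998% or 99.99998% with daily, hourly or 30-s units.

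The specificity for sinus rhythm >1 h is a lesser matter. It has a unit, but its value shifts with how follow-up is segmented: 93.3% to 99.1% under the assumed 5 to 100 episodes per AFib patient when unbroken stretches are counted.

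The primary per-patient specificity, its stated precision and the sample size are unaffected. The change is worth making because no listed measure counts false alarms per monitored time, and the data for one are already collected.

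**What to change.** In Secondary objectives, keep the episode-level sensitivities. Replace the specificity for any AFib episode with:

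- **(a) A false-alarm rate:** watch AFib detections that do not overlap recorder AFib, per 1,000 analyzable hours of recorder time without AFib. Give a patient-level interval (negative binomial or patient bootstrap), because alarms repeat within patients. Using analyzable hours also keeps unworn time, which the full analysis set rates as no AFib signal, from counting as correct negatives.
- **(b) Episode-level positive predictive value:** the share of watch AFib episodes that overlap recorder AFib.

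If the specificity for sinus rhythm >1 h is kept, compute it on windows of one fixed length and print that length beside the figure. Amend the interval sentence in Statistical methods and analysis populations to match.

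The cost is wording in two sections and slightly more analysis work on the same uploaded data. The published figure will look less favourable than a specificity near 100%.
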